### Model Comparison and Performance Metrics

To evaluate the performance of all predictive models, receiver operating characteristic (ROC) analysis will be conducted on the 2 testing cohorts. An overall measure of predictive performance is represented by the area under the ROC curve. Moreover, we will calculate the measures of diagnostic accuracy, such as sensitivity, specificity, positive predictive value, and negative predictive value. These specific measures are determined by setting thresholds on each ROC curve. To achieve optimal balance between sensitivity and specificity, we will select the cut-off points closest to the plot area’s upper-left corner. The 95% CIs for each model or score will also be reported and compared.

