### Predictive Modelling for Clinical Decision Making

In this study, we will develop and validate a novel interpretable triage system for risk stratification of patients in the ED. Our proposed solution will be compared with baseline risk prediction tools such as traditional clinical scores and black box machine learning models. The extracted data set will be split into training, validation, and testing sets to build and validate the predictive models. The ED visit episodes from January 1, 2008, to December 31, 2018, will be randomly divided into 2 non-overlapping cohorts: a training cohort (80%) and a validation cohort (20%). The ED visits dated in 2019 are assigned to one testing cohort, while those dated in 2020 are assigned to a second testing cohort covering the period of the COVID-19 pandemic [40,41]. Using this sequential testing design, we will be able to test whether the population shift and the COVID-19 pandemic would impact model performance [42]. Further details are presented below.

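### Cut-offs re-chosen on each testing cohort's own ROC curve cannot show how a pre-set cut-off holds up in 2019 and 2020

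*Protocol article*

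**What the plan says.** Under Predictive Modelling for Clinical Decision Making, visits from 2008 to 2018 are split at random into training (80%) and validation (20%) cohorts. Later visits are held out by year: "The ED visits dated in 2019 are assigned to one testing cohort, while those dated in 2020 are assigned to a second testing cohort". The stated purpose is that "we will be able to test whether the population shift and the COVID-19 pandemic would impact model performance".

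Under Model Comparison and Performance Metrics, "receiver operating characteristic (ROC) analysis will be conducted on the 2 testing cohorts". The summary measure is AUC: "An overall measure of predictive performance is represented by the area under the ROC curve". Beyond that, "we will calculate the measures of diagnostic accuracy, such as sensitivity, specificity, positive predictive value, and negative predictive value". The cut-off for those four measures is specified in two steps: "These specific measures are determined by setting thresholds on each ROC curve", and "we will select the cut-off points closest to the plot area’s upper-left corner". Finally, "The 95% CIs for each model or score will also be reported and compared".

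No other section carries a decision cut-off on the total score forward from the 2008–2018 data. The cut-off values in AutoScore module 5 (Proposed Method: Interpretable SERT) are for categorising continuous predictors and are not decision thresholds.

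**The concern.** The only ROC curves that the metrics section describes are those on the testing cohorts. On a plain reading, the corner cut-off is therefore chosen afresh for each model in each testing cohort, using that cohort's outcomes.

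A cut-off set in advance cannot be tuned to outcomes that have not yet occurred. If scores run higher or lower in 2020 than in earlier years, a pre-set cut-off flags more or fewer patients, and its sensitivity and specificity move. Re-selecting the cut-off on the 2020 curve moves the threshold along with the scores and removes that effect from the report. AUC does not bring it back, because it depends only on the ranking of patients within a cohort.

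At stake is the comparison between 2019 and 2020. Near-identical sensitivity and specificity in the two years could be read as stable performance even where a threshold chosen on earlier data would have behaved quite differently.

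**Working it through.** The article states no AUC, cut-off or expected drift, so there is no figure to reproduce. The check below tests the mechanism under stated assumptions.

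**Inputs from the article.** Corner rule applied on the testing-cohort curves; 2019 and 2020 evaluated separately; more than 120,000 visits a year (Study Setting); about 650,000 admissions in 1.8 million visits (Results), which is 650,000 / 1,800,000 = 36%.

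**Assumptions.** Scores normal with SD 1 in events and non-events, means d apart; AUC 0.75 to 0.85; in 2020 all scores rise by a common amount s of 0.3 to 0.5 SD; event rates of 0.5% and 2% for rare outcomes; 120,000 visits per testing cohort.

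**Formulas.** AUC = Φ(d/√2). The cut-off minimising (1 − sens)² + (1 − spec)² is c = d/2 above the non-event mean, which gives sens = spec = Φ(d/2). After a common shift s:

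- Re-selected cut-off: it moves to c + s, so sens = spec = Φ(d/2) again, and AUC is unchanged.
- Locked cut-off: sens = Φ(d/2 + s), spec = Φ(d/2 − s).

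**Results for an upward shift.**

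| AUC | d/2 | Re-selected sens/spec, both years | Locked, s = 0.3 | Locked, s = 0.5 | Fall in locked specificity |
|---|---|---|---|---|---|
| 0.75 | 0.477 | 0.683/0.683 | 0.781/0.570 | 0.836/0.491 | 0.113 to 0.192 |
| 0.80 | 0.595 | 0.724/0.724 | 0.815/0.616 | 0.863/0.538 | 0.108 to 0.186 |
| 0.85 | 0.733 | 0.768/0.768 | 0.849/0.667 | 0.891/0.592 | 0.101 to 0.176 |

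A downward shift mirrors this, and sensitivity is what falls: at AUC 0.80 and s = −0.5, the locked values are 0.538/0.863. With an unchanged event rate, the re-selected PPV and NPV do not move either. At AUC 0.80 and 36% events they stay at 0.596 and 0.824, whereas at the locked cut-off with s = 0.5 they become 0.512 and 0.875.

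**What the planned measures do detect.**

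- Discrimination: a fall in AUC from 0.80 to 0.76 shows in the AUC itself and takes re-selected sens and spec from 0.724 to 0.691. With Hanley–McNeil standard errors at AUC 0.80, the difference between two independent cohorts detectable with 80% power (two-sided 5%) is (1.96 + 0.84) × √2 × SE. This gives 0.006 at 36% events (SE 0.00141), 0.022 at 2% (SE 0.00546) and 0.043 at 0.5% (SE 0.0109).
- Event rate: at AUC 0.80, the re-selected PPV goes from 0.051 to 0.075 when the event rate rises from 2% to 3%.

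**Optimism from choosing the cut-off on the test data.** By simulation with 120,000 visits, the inflation of sens + spec is about 0.0009 at 36% events, 0.0015 at 2% and 0.009 at 0.5%.

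**The case against.** The strongest reply is that AUC is the declared overall measure, that it is estimated separately in 2019 and 2020 with confidence intervals, and that the cohorts are large enough to detect modest losses of discrimination. PPV and NPV are planned too, and they respond to a changed event rate. All of this stands. A reader might infer that the design cannot show any population or pandemic effect, or that every planned summary is blind to drift; the documents do not support that.

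Second, a reader might infer that the reported accuracy is seriously overfitted. It is not: the models are built on 2008–2018 data only, and the optimism from the cut-off alone is at most about 0.009 in sens + spec under the rates assumed here.

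Third, a reader might treat the absence of a calibration measure as the error. The article condenses a fuller plan, and its list of accuracy measures is open-ended, so that absence cannot carry the point.

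Fourth, the article names no operating cut-off for clinical use, and the corner rule does put scores on different scales at a comparable point. That is a fair reason to show corner cut-offs descriptively, and it means that no claim about mis-triage in practice follows. It does not answer the narrower problem. The article chose to report threshold-based measures, and it stated a rule that removes one kind of shift from them.

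Some ambiguity remains: the text does not literally say one cut-off per cohort. No other ROC curve is described in that section, however, so this is the plain reading.

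**Conclusion.** The point holds in limited form. As stated, the threshold rule prevents sensitivity and specificity from showing how a pre-set cut-off performs in 2019 and 2020, and so leaves part of the stated aim of the sequential design unmet. Because the article fixes the rule explicitly, this is not detail left to a fuller document.

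Under a binormal score with AUC 0.75 to 0.85 and a common upward shift of 0.3 to 0.5 SD, the planned values stay exactly where they were, while specificity at a locked cut-off falls by about 0.10 to 0.19 and sensitivity rises. These sizes rest on assumed inputs, and the real shift may be smaller, larger, downward or not common to all patients. The mechanism does not depend on the particular values. The harm is masked drift at a fixed cut-off, not overfitting. The change should be made before the test results are produced.

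**What to change.** For each score and outcome, choose the cut-off once on the 20% validation cohort from 2008–2018, by the same corner rule if that is preferred. Freeze it, apply it unchanged to 2019 and 2020, and report sensitivity, specificity, PPV and NPV with 95% CIs at that cut-off in both cohorts. Do the same for the baseline models and scores, so that comparisons stay like for like. Cut-offs re-optimised on a testing cohort may still be shown if labelled descriptive.

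Reporting observed/expected risk and the calibration slope in each testing cohort would be a useful addition for the shift question, though its absence is not the defect.

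The cost is small. The validation cohort already exists, the article says that data are still being linked and cleaned, and no new data are needed. It means a little more analysis, and reported accuracy may look slightly less favourable.

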#### Baseline Methods: Traditional Clinical Scores

Several traditional clinical scores will be calculated for performance comparison with the SERT scores. They are the PACS triage system [32], Modified Early Warning Score [44], National Early Warning Score [45], Rapid Acute Physiology Score [46], Rapid Emergency Medicine Score [47], and Cardiac Arrest Risk Triage [48].

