### Significance

The identification of patients’ risk at an early stage allows for better resource allocation. There is particular significance in this point because the instability of vital signs may occur later in the ward, leaving a limited time window for life-saving action or decision making, which can be especially difficult in a busy hospital. Patient groups at high risk should be identified earlier in the ED and, if possible, flagged for more stringent monitoring. Similarly, low-risk patients may require less intensive monitoring and treatment, thereby saving hospital resources. The SERT system that we propose has the potential to provide a feasible solution. This system allows medical personnel to assess patient risk at multiple decision points based on various clinical and nonclinical factors. In a dynamic way, SERT measures risk sequentially and in a manner that is perfectly suited to actual clinical needs.

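### The upper-left-corner cut-off fixes an unjustified, outcome-blind trade-off and a different operating point for each model, so sensitivity, PPV and NPV alone do not rank SERT against the other scores

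*Protocol article*

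**What the plan says.** The rule is in the protocol article under Model Comparison and Performance Metrics. The AUC comes first: "An overall measure of predictive performance is represented by the area under the ROC curve". The accuracy measures follow: "These specific measures are determined by setting thresholds on each ROC curve". The criterion and its reason are "To achieve optimal balance between sensitivity and specificity" and "we will select the cut-off points closest to the plot area’s upper-left corner". Intervals are then promised: "The 95% CIs for each model or score will also be reported and compared". No other operating point, minimum sensitivity or relative cost of errors is named.

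The rule covers every outcome in Proposed Method: Interpretable SERT, which run from admission and 2-day mortality (SERT-1) to 7/30-day mortality, ICU transfer and prolonged stay (SERT-3).

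The comparison is a stated aim. Objective promises it against traditional triage tools, and Baseline Methods: Traditional Clinical Scores says "Several traditional clinical scores will be calculated for performance comparison with the SERT scores". One of those scores, PACS, has four levels (Study Setting). Significance, in the Discussion, foresees that "low-risk patients may require less intensive monitoring and treatment, thereby saving hospital resources".

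**The concern.** There are two difficulties.

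First, the criterion does not look at the outcome. The distance to the corner depends only on the two error rates. Event rate and the consequence of each error do not enter, so admission and 2-day death get the same treatment. Yet the use foreseen in Significance makes the two errors unequal: a missed event among patients who are monitored less is not the mirror image of an unnecessary flag.

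Second, each curve gets its own threshold. The resulting sensitivity, PPV and NPV reflect the shape of the curve as well as discrimination, and for a four-level score they also reflect where the levels happen to fall. A sensitivity above or below that of PACS or an early warning score may only mean that a different share of patients was flagged. The comparison with current triage is where this matters most, because PACS can be cut at only three places.

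The point concerns the criterion itself and holds whichever cohort the cut-off is chosen on.

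**Working it through.** **Inputs.** The article gives no AUC, sensitivity or mortality rate, so there is no stated figure to reproduce. AUCs, curve shapes and death rates below are assumptions. From the article: about 650,000 admissions in 1.8 million visits (Results), so admission prevalence is 650,000/1,800,000 = 36%; PACS has four levels, so three usable cut-offs.

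**1. Where the corner point falls.** The rule minimises (1 − sens)² + (1 − spec)². For an equal-variance binormal curve, d = √2·Φ⁻¹(AUC), and the minimum is at sens = spec = Φ(d/2). At AUC 0.85, d = 1.466 and Φ(0.733) = 0.768.

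| Assumed AUC | Sens = spec | Events below cut-off |
|---|---|---|
| 0.70 | 0.645 | 36% |
| 0.75 | 0.683 | 32% |
| 0.80 | 0.724 | 28% |
| 0.85 | 0.768 | 23% |
| 0.90 | 0.818 | 18% |
| 0.95 | 0.878 | 12% |

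If the SD ratio of cases to controls varies from 0.7 to 1.5, the share below the cut-off is 27–35% at AUC 0.75, 24–30% at 0.80, 20–25% at 0.85 and 16–20% at 0.90.

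**2. The implied trade-off.** A cut-off is cost-optimal when C_FN/C_FP = (1 − p)/(p × slope), where slope is the ROC slope there and p is prevalence. At the symmetric corner point the slope is 1.

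- p = 0.5% (assumed): 0.995/0.005 = 199 false alarms per missed event.
- p = 1% (assumed): 99.
- p = 5% (assumed): 19.
- p = 36% (admission): 0.64/0.36 = 1.8.

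So the exchange rate is set by prevalence. It also differs between models. At the corner the slope equals (1 − spec)/(1 − sens). At AUC 0.80 this is 0.300/0.237 = 1.27 for SD ratio 0.7 and 0.230/0.302 = 0.76 for SD ratio 1.5. At p = 0.5% the implied ratios are about 157 and 261.

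**3. Comparison across models.** Corner points for three assumed curves:

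| AUC | SD ratio | Sens | Spec |
|---|---|---|---|
| 0.80 | 0.7 | 0.763 | 0.700 |
| 0.80 | 1.5 | 0.698 | 0.770 |
| 0.77 | 0.7 | 0.743 | 0.672 |

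The two curves with equal AUC differ by 6.5 percentage points in sensitivity. The AUC 0.77 curve shows higher sensitivity than the second AUC 0.80 curve.

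A four-level score on a latent AUC of 0.80 was tried with three placements of its levels. The best available corner point had sens/spec 0.614/0.816, 0.862/0.540 and 0.883/0.500. Discrimination of the underlying scale was the same each time.

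**4. PPV and NPV.** At AUC 0.85 and an assumed 0.5% death rate:

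- PPV = 0.768 × 0.005 / (0.768 × 0.005 + 0.232 × 0.995) = 1.6%.
- NPV = 0.768 × 0.995 / (0.768 × 0.995 + 0.232 × 0.005) = 99.8%.

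The NPV is close to 100% although 23% of deaths lie below the cut-off.

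**5. What the corner row does not show.** At sensitivity S, specificity = Φ(d − Φ⁻¹(S)). For illustration at S = 95%, specificity is 0.25, 0.33, 0.43 and 0.57 at AUC 0.75, 0.80, 0.85 and 0.90.

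**The case against.** The strongest defence is that the corner rule is a recognised descriptive convention used here for its stated purpose of balance. The AUC is named as the overall measure and needs no threshold. Sensitivity is reported beside specificity, so the pair can be read together, and the reported sensitivity itself discloses the share of events missed. A condensed article may also leave extra operating points to a fuller plan. The remarks on AUC and on reading the pair stand, and they limit the point to the threshold-based measures. The last remark does not answer it: the article states this rule and names no other.

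Three stronger readings are tempting, and the article does not support them.

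- A reader might infer that a missed death counts the same as one false alarm. It is the error rates that are treated symmetrically. With a rare outcome the implied exchange is many false alarms per missed event, as step 2 shows.
- A reader might infer that a fifth to a third of deaths would be labelled low risk. The article uses the cut-off only to compute accuracy measures, and Significance names no threshold. Strengths describes an app that returns a score. The range itself needs an AUC of about 0.73 to 0.88 under the binormal assumption.
- A reader might infer that the scores cannot be compared at all. AUCs and sensitivity–specificity pairs can be.

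A practical objection also stands. PACS usually cannot be read at a chosen sensitivity, integer scores have ties, PACS flag rates suit SERT-3 poorly because it applies to admitted patients, and matching a flag rate equalises workload without limiting missed events. The remedy has to allow for all four.

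**Conclusion.** The point holds in limited form. The stated rule fixes one outcome-blind trade-off for every endpoint, leaves the implied exchange rate to prevalence and curve shape without justification, and puts each model at its own operating point. Sensitivity, PPV and NPV at that point therefore do not by themselves rank SERT against PACS or the early warning scores. The AUC comparison is untouched.

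On size, the share of events below the reported cut-off would be about 12% to 36% over assumed AUCs of 0.95 down to 0.70, and sensitivity can order two models opposite to their AUCs. These figures rest on binormal curves and assumed AUCs, and the PPV, NPV and mortality trade-off figures also rest on assumed death rates. They illustrate the behaviour of the rule and do not predict this study's results. The change is worth making because the comparison with current triage is a stated aim and a better basis for it costs little.

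**What to change.** Keep the upper-left point as a supplementary row and make a common operating point the main threshold-based comparison.

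- **SERT-1 and SERT-2:** report every score's sensitivity, specificity, PPV and NPV at the proportion of patients flagged by PACS-1 and at the proportion flagged by PACS-1/2. For tied integer scores use the nearest attainable cut-off or interpolation, and show the flag rate achieved.
- **SERT-3:** use a common specificity or a common flag rate among admitted patients instead.
- **Mortality outcomes:** also report specificity and proportion flagged at one pre-specified high sensitivity for the finely graded models, with PACS shown at its own three cut-offs. Equal flag rates alone do not limit missed events, so this row is needed alongside them.

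These are reporting points for comparing models and do not set a clinical threshold. No new data or refitting is needed. The cost is some wording and a few extra table rows, and specificity at high sensitivity will look less favourable than at the corner (at AUC 0.85, about 0.43 at 95% sensitivity against 0.77).

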### Statistical Analysis

We will perform data analysis using R version 4.0 (R Core Team). When summarizing descriptive results, frequency and percentages are reported for categorical variables, while means and SDs are reported for continuous variables. For categorical variables, the chi-square test or Fisher exact test will be used. For numeric variables, the *t* test will be applied. Further, univariable and multivariable logistic regressions will be used to identify common risk factors associated with the outcomes.

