## Results

The raw data have been extracted, and we are currently linking and cleaning the data. In the data extraction process, we included all patients who visited the ED at Singapore General Hospital between January 1, 2008, and December 31, 2020. Patients under the age of 21 years were excluded. If the patients were admitted through the corresponding ED visit, they would be followed throughout their inpatient stay. The data set contains more than 1.8 million ED visit episodes of over 810,000 unique patients. Approximately 650,000 of these ED visits resulted in subsequent hospitalizations. Our findings and modelling results are expected to be published by 2022.

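### Models are compared through each model's own 95% CI, although all are scored on the same test visits; the plan should give a paired AUC difference with its interval

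*Protocol article*

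**What the plan says.** The section Model Comparison and Performance Metrics sets the common evaluation: "To evaluate the performance of all predictive models, receiver operating characteristic (ROC) analysis will be conducted on the 2 testing cohorts". The summary measure is the AUC: "An overall measure of predictive performance is represented by the area under the ROC curve". The section closes with the only statement on how uncertainty enters the comparison: "The 95% CIs for each model or score will also be reported and compared". No interval or test for a difference between two AUCs is named.

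The comparators are six clinical scores ("Several traditional clinical scores will be calculated for performance comparison with the SERT scores") and, in the next section, random forest, LASSO and deep learning. The Objective names the comparison of SERT with both groups as part of the study.

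The unit throughout is the ED visit. Under Predictive Modelling for Clinical Decision Making, "The ED visit episodes from January 1, 2008, to December 31, 2018, will be randomly divided into 2 non-overlapping cohorts", and "The ED visits dated in 2019 are assigned to one testing cohort, while those dated in 2020 are assigned to a second testing cohort". The Results section reports that "The data set contains more than 1.8 million ED visit episodes of over 810,000 unique patients". The Statistical Analysis section adds that "univariable and multivariable logistic regressions will be used to identify common risk factors associated with the outcomes". The article gives neither a method for the intervals nor any statement on repeat visits. Study Cohort and Design lists a patient identifier.

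**The concern.** The precision of a difference between two AUCs from the same visits depends on their covariance. A visit that is easy or hard for one score tends to be so for the other, so the difference is usually known much more precisely than either AUC alone. Two separate intervals contain no information on this. A reader who is given only those intervals will look at whether they overlap, and for correlated AUCs that is a very insensitive check.

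What is at stake is the SERT-against-baseline result. A real advantage of a black box model over SERT, or of SERT over an established score, could sit inside overlapping intervals and be taken for no difference.

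A second, smaller matter concerns the same intervals. Patients contribute more than one visit. If intervals and standard errors were computed per visit without regard to this, they would come out somewhat too narrow, which is the opposite direction.

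**Working it through.** The article states no AUC, standard error or power, so there is no figure of its own to reproduce. The check works out the consequences.

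**Inputs from the article.** 1.8 million visits over 13 years: 1,800,000 / 13 = about 138,500 visits in one testing year. Admissions: 650,000 / 1,800,000 = 36.1% of visits. Visits per patient: 1,800,000 / 810,000 = 2.22 over 13 years.

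**Assumed, not in the article.** AUCs of 0.80 and 0.82; correlation r between them; event rates of 1% and 0.2% for rare outcomes; visits per patient within one year, their squared coefficient of variation (CV²), and the intraclass correlation (ICC).

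**1. Relative loss, equal standard errors.** Non-overlap of two 95% CIs needs a gap above 2 × 1.96 × SE = 3.92 SE. A paired 95% CI excludes zero at 1.96 × SE × √(2(1−r)). The ratio is 2 / √(2(1−r)):

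- r = 0.5: 2 / 1.000 = 2.00
- r = 0.7: 2 / 0.775 = 2.58
- r = 0.8: 2 / 0.632 = 3.16

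If the true gap gives the paired analysis 90% power, it equals (1.96 + 1.28) × SE × √(2(1−r)). The chance of non-overlap is then 1 − Φ(3.92 / √(2(1−r)) − 3.24), which is 25%, 3% and 0.2% for the three values of r.

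**2. Absolute loss in one testing year.** The Hanley-McNeil formula is SE² = [A(1−A) + (n1−1)(Q1−A²) + (n0−1)(Q2−A²)] / (n1·n0), with Q1 = A/(2−A) and Q2 = 2A²/(1+A). The gap needed is 1.96(SE1 + SE2) for non-overlap and 1.96√(SE1² + SE2² − 2r·SE1·SE2) for the paired interval.

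| Outcome rate | SE1, SE2 | Non-overlap | Paired, r = 0.5 | Paired, r = 0.7 |
|---|---|---|---|---|
| 36.1% (admission) | 0.00131, 0.00126 | 0.0050 | 0.0025 | 0.0020 |
| 1% (assumed) | 0.00718, 0.00694 | 0.028 | 0.014 | 0.011 |
| 0.2% (assumed) | 0.01603, 0.01550 | 0.062 | 0.031 | 0.024 |

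With 120,000 visits instead, the admission row becomes 0.0054 against 0.0027 and 0.0021.

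**3. Simulation.** Two equally good scores were compared in 1,000 replicates of about 6,000 visits, with an AUC correlation of about 0.60. The overlap rule rejected 0.0% of true nulls. A paired DeLong comparison computed per visit rejected 4.2% when the scores had no patient-level correlation, and 6.3% to 6.6% when they had it. Coverage of a single per-visit AUC interval fell from 94.8% to about 93.2% under strong clustering.

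**4. Size of the clustering effect.** The design effect is 1 + ((1 + CV²)m − 1) × ICC, with ICC assumed at 0.05 to 0.30.

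- One testing year, m = 1.4 and CV² = 0.4 (both assumed): 1.4 × 1.4 − 1 = 0.96, so the design effect is 1.05 to 1.29 and the standard error is 1.02 to 1.13 times the per-visit one.
- All 13 years, m = 2.22 and CV² = 0.55 (CV² assumed): 1.55 × 2.22 − 1 = 2.44, so the design effect is 1.12 to 1.73 and the standard error is 1.06 to 1.32 times the per-visit one.

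**The case against.** The article says that intervals will be compared; it does not say that non-overlap is the criterion. It states no equivalence or non-inferiority claim and no margin. The case that it makes for SERT is transparency and ease of use, not equal accuracy. All of this is correct. The power figures therefore describe the natural way to read separate intervals, not a rule that the article adopts. It remains true that the only comparison named cannot give the uncertainty of a difference, whatever reading rule is used.

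Three stronger readings are tempting and are not supported.

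- A reader might infer that the models' own error bars are wrong because the AUCs are paired. They are not: pairing leaves each single interval valid and affects only inference drawn from setting two of them side by side.
- A reader might infer from the visit-level unit and the standard tests that visits are declared independent. The article gives no interval method or variance estimator, and a condensed article may leave these to a fuller plan. The clustering part is therefore a precaution, not an error shown.
- A reader might infer that clustering matters most for rare outcomes. That is doubtful: a patient dies once, so 2-day deaths come almost entirely from different patients, and with a rare outcome the cases drive most of the AUC's variance.

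It is also fair that 2.22 visits per patient is a 13-year average while each testing cohort covers one year. The design-effect formula will moreover tend to overstate the inflation for covariates that change from visit to visit.

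**Conclusion.** The point holds for the comparison of models. Comparing separate intervals on shared test visits gives no interval for the difference and, if read through overlap, needs a gap 2.0 to 3.2 times that of a paired analysis (equal standard errors, assumed correlation 0.5 to 0.8).

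For admission the extra gap is at most about 0.003 AUC (0.0050 − 0.0020) and of little practical weight. For rare outcomes it could matter: at an assumed 0.2% event rate and r = 0.5, black box advantages between about 0.03 and 0.06 AUC would be detectable by a paired interval but could be hidden by overlapping ones. These larger losses rest on event rates that the article does not give.

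Repeat visits are a secondary reason to choose a patient-level method. Their effect within one testing year is probably modest, about 1.02 to 1.13 times the standard error, and that range rests on an assumed ICC and visit distribution.

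**What to change.** In Model Comparison and Performance Metrics, replace the comparison of separate intervals with the following: for each outcome and each testing cohort, the AUC difference (SERT minus comparator) is estimated on the same visits and reported with a 95% CI. Obtain that interval from a bootstrap that draws patients by Patient ID, takes all of a drawn patient's visits in that cohort together, and recomputes both AUCs in each resample. Each model's own interval can still be reported, from the same resamples.

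In Statistical Analysis, state that the risk-factor logistic regressions use patient-clustered (sandwich) standard errors.

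The data are extracted and still being linked and cleaned, and the patient identifier is in the data set, so no new data are needed. The cost is a little more analysis code, and single-model intervals that become slightly wider.
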